| Name of sponsor:
Statens Serum Institut                                                                                                                   |                                                                                                                                                                                                                                                                                                                                                                                                                                                                                                                                                                                                                                                                                                                                                                                                                                                                                                                                                                                                                                                                                                                                                                                                                                                                                                                                                                                                                                                                                                                                                                                                                                                                                                                                                                                                                                                                                                                                                                                                                                                                                                                                                                                                                                                                                                                                                                                                                                                                                                                                                                                                                                                                                                                                                                                                                            | TESEC-03

FINAL Version |
| Finished product: C-Tb                                                                                                                                       |                                                                                                                                                                                                                                                                                                                                                                                                                                                                                                                                                                                                                                                                                                                                                                                                                                                                                                                                                                                                                                                                                                                                                                                                                                                                                                                                                                                                                                                                                                                                                                                                                                                                                                                                                                                                                                                                                                                                                                                                                                                                                                                                                                                                                                                                                                                                                                                                                                                                                                                                                                                                                                                                                                                                                                                                                            |                                             |
| Name of active ingredient:
Recombinant dimer of 6 kDa early secretory antigen target (rdESAT-6) and recombinant 10 kDa culture filtrate protein (rCFP-10) |                                                                                                                                                                                                                                                                                                                                                                                                                                                                                                                                                                                                                                                                                                                                                                                                                                                                                                                                                                                                                                                                                                                                                                                                                                                                                                                                                                                                                                                                                                                                                                                                                                                                                                                                                                                                                                                                                                                                                                                                                                                                                                                                                                                                                                                                                                                                                                                                                                                                                                                                                                                                                                                                                                                                                                                                                            |                                             |
| Exclusion criteria:                                                                                                                                          | The volunteer: 

1. Has a history of tuberculosis or has been in close contact to a person with active tuberculosis within 5 years from trial inclusion

2. Has a positive QuantiFERON®-TB Gold In-Tube assay at inclusion

3. Laboratory parameters outside of normal range judged by site investigator to be clinically significant

4. Has within 3 months prior to the day of inclusion been in treatment with a product which is likely to modify the immune response (e.g., immunoglobulin, systemic corticosteroids, methotrexate, azathioprine, cyclosporine or blood products)

5. Has been vaccinated with a live vaccine within 6 weeks prior to the day of inclusion (e.g. MMR, yellow fever, oral typhoid vaccines)

6. Has been vaccinated with BCG < 6 months prior to the day of inclusion

7. Has been tuberculin (TST) tested < 6 months prior to the day of inclusion

8. Has a known congenital or acquired immune deficiency

9. Has an active disease affecting the lymphoid organs (e.g., Hodgkin’s disease, lymphoma, leukaemia, sarcoidosis)

10. Is infected with HIV

11. Has a current skin condition which interferes with the reading of the skin tests e.g. tattoos, severe scarring, burns/sunburns, rash, eczema, psoriasis, or any other skin disease at or near the injection sites

12. Has a condition where blood drawings pose more than minimal risk for the volunteer, such as haemophilia, other coagulation disorders, or significantly impaired venous access

13. Currently participating in another clinical trial with an investigational or non investigational drug or device, or has participated in another clinical trial within the 3 months prior to dosing

14. Has participated in previous clinical trials investigating the ESAT-6 and/or CPP-10 antigens

15. Is pregnant, breast-feeding or intending to get pregnant

16. Is a female not willing to use effective barrier (including spermicidal gel), hormonal or intrauterine contraceptive measures

17. Has a history of alcohol, narcotic, benzodiazepine, or other substance abuse or dependence within the 12 months preceding Visit 1

18. Has a positive urine drug screen at Visit 1 and Visit 2 (i.e., amphetamines, barbiturates, benzodiazepines, cannabinoids, cocaine, or opiates)

19. Has a positive alcohol breath test at Visit 1 and Visit 2. [NOTE: subjects must be told to avoid consumption of alcoholic beverages for at least 24 hours prior to attending the Centre]

20. Has a condition which in the opinion of the investigator is not suitable for participation in the study

 |                                             |

[figure not shown]

|                                                                                                                                                                     |                                                                                                                                                                                                                                                                                                                                                                                                                                                                                                                                                                                                                                                                                                                                                                                                                                                                                                                                                                                                                                                                                                                                                                                                                                                                                                                                               |                                             |
|---------------------------------------------------------------------------------------------------------------------------------------------------------------------|-----------------------------------------------------------------------------------------------------------------------------------------------------------------------------------------------------------------------------------------------------------------------------------------------------------------------------------------------------------------------------------------------------------------------------------------------------------------------------------------------------------------------------------------------------------------------------------------------------------------------------------------------------------------------------------------------------------------------------------------------------------------------------------------------------------------------------------------------------------------------------------------------------------------------------------------------------------------------------------------------------------------------------------------------------------------------------------------------------------------------------------------------------------------------------------------------------------------------------------------------------------------------------------------------------------------------------------------------|---------------------------------------------|
| Name of sponsor:
Statens Serum Institut                                                                                                                   |                                                                                                                                                                                                                                                                                                                                                                                                                                                                                                                                                                                                                                                                                                                                                                                                                                                                                                                                                                                                                                                                                                                                                                                                                                                                                                                                               | TESEC-03

FINAL Version |
| Finished product: C-Tb                                                                                                                                       |                                                                                                                                                                                                                                                                                                                                                                                                                                                                                                                                                                                                                                                                                                                                                                                                                                                                                                                                                                                                                                                                                                                                                                                                                                                                                                                                               |                                             |
| Name of active ingredient:
Recombinant dimer of 6 kDa early secretory antigen target (rdESAT-6) and recombinant 10 kDa culture filtrate protein (rCFP-10) |                                                                                                                                                                                                                                                                                                                                                                                                                                                                                                                                                                                                                                                                                                                                                                                                                                                                                                                                                                                                                                                                                                                                                                                                                                                                                                                                               |                                             |
| Investigational diagnostic agent:                                                                                                                            | Investigational product C-Tb (rdESAT-6 + rCFP-10):
rdESAT-6..... 0.5 µg
rCFP-10..... 0.5 µg
Disodium hydrogen phosphate dehydrate ..... 1.4 mg
Potassium dihydrogen phosphate ..... 0.2 mg
Potassium chloride ..... 0.2 mg
Sodium chloride ..... 8.0 mg
Polysorbate 20..... 0.1 µL
Phenol..... 0.5 %
Water for injections..... up to 1 mL                                                                                                                                                                                                                                                                                                                                                                                                                                                                                                                                                                                                                                                                                                                                                                                                                                                                                                                                                                   |                                             |
| Active reference diagnostic agent:                                                                                                                           | 2 T.U. Tuberculin PPD RT 23 SSI – 0.1 mL                                                                                                                                                                                                                                                                                                                                                                                                                                                                                                                                                                                                                                                                                                                                                                                                                                                                                                                                                                                                                                                                                                                                                                                                                                                                                                      |                                             |
| Dosage and route of administration:                                                                                                                          | 
0.1 mL of the investigational diagnostic agent (C-Tb) is administered to the RIGHT or LEFT forearm as indicated by the randomisation code and 0.1 mL of the reference agent (2 TU PPD) is administered to the opposite forearm.
 
The two injections will be administered intradermally by the Mantoux technique into the flexor surface of the RIGHT/LEFT forearm at the junction of the upper third with the lower two-thirds. A 1 mL syringe fitted with a short bevelled needle (insulin needle) is used for the injection of the skin test agents.
 
The w:w ratio of rdESAT-6 and rCFP-10 (C-Tb) is 1:1 in the solution. A dose of 0.1 µg C-Tb refers to a test solution consisting of 0.05 µg rdESAT-6 and 0.05 µg rCFP-10 per 0.1 mL.
                                                                                                                                                                                                                                                                                                                                                                                                                                                                                                                                                                                |                                             |
| Statistical methods:                                                                                                                                         | 
The main objective of the trial is to contribute information on the size of induration in a healthy BCG vaccinated population, which can be used to define an optimal cut-off point for a C-Tb skin test.
 
In the trial the specificity of C-Tb (Specx) as a function of x (the diameter of the induration in mm) will be estimated.
 
For each (integer) value of x, Specx is estimated by the relative frequency of volunteers in the trial with a C-Tb induration ≤ x mm. 95% confidence intervals for Specx are obtained as Specx ± 2 × √ (Specx × (1 - Specx) / n), where n is the number of validly included volunteers.
 
As BCG vaccinated healthy subjects are not supposed to get an induration when exposed to C-Tb no formal statistical comparison of induration sizes between C-Tb and PPD will be made.
 
The subjects will have their PPD indurations classified according to UK standards for PPD cut-off points: 0-5 mm, 6-14 mm and 15+ mm (The Green Book).
 
PPD is considered negative if the induration is < 6 mm.
 
www.dh.gov.uk/en/PublicHealth/Healthprotection/Immunisation/Greenbook/DH_4097254
 |                                             |

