| Trial objectives:                                                                                                                                            | Primary objectives: 

To assess the specificity of the C-Tb test as a function of the cut-off value (i.e., the smallest size of induration measured in mm resulting in a negative outcome of the C-Tb test) when the test is administered intradermally by the Mantoux technique to healthy BCG vaccinated adults

 
The specificity of the C-Tb test is defined as the relative frequency of subjects in a healthy population (i.e., no exposure to MTb) who have an induration response < cut-off after a C-Tb test.
 
Similarly the sensitivity is defined as the relative frequency of patients with an induration response ≥ cut-off in TB patients.
 
An optimal cut-off point of being infected will be determined by combing the results from the present specificity study with those from a parallel sensitivity study in patients recently diagnosed with TB.
 Secondary objectives: 

To compare the induration response of C-Tb with the induration response of 2 T.U. Tuberculin PPD RT 23 SSI

To compare the induration response of C-Tb with the in-vitro IFN-γ response measured at screening and 28 days after the injections of the skin test agents using the QuantiFERON®-TB Gold In-Tube assay

To record all adverse events occurring within 28 days after application of the agents.

 |                                             |

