## Appendices

Appendix 1: Declaration of Helsinki

Appendix 2: Indemnity Statement

Appendix 3: CIOMS form

Appendix 4: Insurance certificate

### 3 List of Abbreviations and Definitions

|               |                                                                         |
|---------------|-------------------------------------------------------------------------|
| ADR           | Adverse Drug Reaction                                                   |
| AE            | Adverse Event                                                           |
| AFB           | Acid fast bacteria                                                      |
| ALP           | Alkaline Phosphatase                                                    |
| ALT           | Alanine aminotransferase                                                |
| AR            | Adverse Reaction                                                        |
| AST           | Aspartate aminotransferase                                              |
| BCG           | Bacille Calmette-Guérin                                                 |
| CA            | Competent Authority                                                     |
| CFP-10        | 10 kDa Culture Filtrate Protein                                         |
| CI            | Confidence Interval                                                     |
| CIOMS         | Council for International Organizations of Medical Sciences             |
| CRA           | Clinical Research Associate                                             |
| CRC           | Clinical Research Centre                                                |
| CRF           | Case Record Form                                                        |
| CTA           | Clinical Trial Application                                              |
| C-Tb          | rdESAT-6 + rCFP10                                                       |
| Cut-off       | The smallest induration diameter (mm) resulting in a positive C-Tb test |
| DOB           | Date of Birth                                                           |
| DTH           | Delayed Type Hypersensitivity                                           |
| DSMB          | Data safety monitoring board                                            |
| DSMP          | Data safety monitoring plan                                             |
| EC            | Ethics Committee                                                        |

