## **7 Trial objectives**

### **7.1 Primary objectives**

- To assess the specificity of the C-Tb test as a function of the cut-off value (i.e., the smallest size of induration measured in mm resulting in a positive outcome of the C-Tb test) when the test is administered intradermally by the Mantoux technique to healthy BCG vaccinated adults.

The specificity of the C-Tb test is defined as the relative frequency of subjects in a healthy population (i.e., no exposure to MTb) who have an induration response < cut-off after a C-Tb

test, whereas the sensitivity is defined as the relative frequency of patients with an induration response  $\geq$  cut-off in TB patients.

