## 12 Data management and statistical analysis

### 12.1 General considerations

A milestone in the clinical development of C-Tb is to determine on optimal cut-off value for the skin test. The cut-off value is defined as the smallest induration diameter that will result in a positive C-Tb "diagnosis". That is, a person is considered C-Tb positive (C-Tb+) if the induration is  $\geq$  cut-off and C-Tb negative (C-Tb) if the induration is  $<$  cut-off.

If a TB patient (latent or active) is denoted as TB+ and a TB-healthy person as TB the performance of a diagnostic test like C-Tb is quantified by its sensitivity, i.e.,  $\text{Prob}\{ \text{C-Tb}^+ \mid \text{TB}^+ \}$  and by its specificity,  $\text{Prob}\{ \text{C-Tb}^- \mid \text{TB}^- \}$ .

A low cut-off value implies a high sensitivity and a low specificity; and a high cut-off value implies a low sensitivity and a high specificity.

Together with a concurrent C-Tb study in recently diagnosed TB patients (TESEC-04) the data from the present study will contribute to define an optimal cut-off value, balancing sensitivity and specificity.

If  $F^-(x) (= \text{Prob}\{\text{induration} \leq x\})$  denotes the (theoretical) distribution function of the induration in a  $TB^-$  population the specificity of the C-Tb skin test is  $F^-(\text{cut-off} - 1)$ .

If  $F^+(x) (= \text{Prob}\{\text{induration} \leq x\})$  denotes the (theoretical) distribution function of the induration in a  $TB^+$  population the sensitivity of the C-Tb skin test is  $1 - F^+(\text{cut-off} - 1)$ .

The main objective in the present trial is therefore to estimate the distribution function  $F^-$ .

The Biostatistics Unit at SSI will be responsible for the data management and the statistical analysis of the trial data.

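### The Synopsis defines the cut-off by the wrong outcome and indexes specificity by x (induration ≤ x) without linking x to the cut-off; the section 9.3.1 formula is inverted

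*Protocol*

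**What the plan says.** The Synopsis (Trial objectives) promises specificity as a function of the cut-off and explains the cut-off as "the smallest size of induration measured in mm resulting in a negative outcome of the C-Tb test". Section 7.1 states the same objective with the opposite outcome: "the smallest size of induration measured in mm resulting in a positive outcome of the C-Tb test". The definitions list in section 3 agrees with section 7.1 ("The smallest induration diameter (mm) resulting in a positive C-Tb test"). So do section 9.3.1 and section 12.1 ("The cut-off value is defined as the smallest induration diameter that will result in a positive C-Tb" result).

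In words, specificity is the same throughout: the "relative frequency of subjects in a healthy population (i.e., no exposure to MTb) who have an induration response < cut-off after a C-Tb" test (section 7.1; also the Synopsis, sections 6 and 8.1). Sensitivity is the share of TB patients at or above the cut-off.

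The Synopsis (Statistical methods) then changes the index. Specificity "as a function of x (the diameter of the induration in mm) will be estimated", and for each integer x it "is estimated by the relative frequency of volunteers in the trial with a C-Tb induration ≤ x mm". A confidence interval of ± 2 standard errors is attached. How x relates to the cut-off is not stated.

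Section 12.1 defines F⁻(x) as the probability of an induration ≤ x and makes its estimation the main objective. It gives specificity as F⁻(cut-off − 1) and sensitivity as 1 − F⁺(cut-off − 1). Section 9.3.1 gives specificity as 1 − F⁻(cut-off − 1). Section 12.5 contains no specificity estimator. Section 12.6 gives the interval again, for F⁻(x).

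**The concern.** The trial exists to deliver specificity by cut-off, to be combined with TESEC-04 sensitivity in a ROC curve. The Synopsis is the only place where an estimator called specificity comes with its confidence interval. It is indexed by x, while the objective a few rows earlier is indexed by the cut-off, and that objective gives the cut-off the wrong outcome. A reader going from objective to method could take x to be the cut-off and report specificity 1 mm away from its definition. The body does not settle the matter cleanly, because one of its two formulas is itself inverted.

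**Working it through.** **The plan's own figure.** Section 12.6 gives SD = √(F(1 − F)/n). With F = 0.5 and n = 150, √(0.25/150) = 0.0408, stated as 0.041. All nine cells of the table reproduce to three decimals. (The text calls 0.5/√n a variance; it is the standard deviation. The table is unaffected.) The precision figures are not in question.

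**The cut-off wording.** Taken literally, the smallest induration giving a negative test is 0 mm. No reading lies below 0, so specificity defined as < cut-off would be 0, and sensitivity defined as ≥ cut-off would be 1. The wording also conflicts with the < and ≥ sentences that follow it in the same Synopsis row.

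**The index.** For whole-millimetre readings, {induration < c} = {induration ≤ c − 1}. Hence:

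- specificity at cut-off c = F⁻(c − 1), as in section 12.1;
- the Synopsis quantity at x = F⁻(x), which is the specificity at cut-off c = x + 1;
- with x = c − 1 the two agree exactly, and the difference is 0;
- with x taken as c, the Synopsis gives F⁻(c) = F⁻(c − 1) + P(induration = c).

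The Synopsis itself shows this relation for PPD: the lowest band ends at 5 mm and negative means < 6 mm, so c = 5 + 1. It does not say so for C-Tb.

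**Size under the misreading.** If k of 150 volunteers read exactly x, the excess is k/150. The protocol gives no induration distribution, so k is an assumption.

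| k (assumed) | Excess, percentage points |
|---|---|
| 0 | 0 |
| 1 | 0.67 |
| 3 | 2.0 |
| 5 | 3.3 |
| 8 | 5.3 |

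For scale, the planned 95% half-width, 2√(p(1 − p)/150), is 4.9 points at p = 0.90, 3.6 at 0.95 and 2.3 at 0.98.

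**The ROC curve.** Suppose specificity is counted as ≤ x and sensitivity as ≥ the same x. For a useless test with identical distributions in both groups, P(X ≥ x) + P(X ≤ x) − 1 = P(X = x), which exceeds 0 wherever readings fall on x. On an invented distribution, used only to show direction, the area under the curve is 0.905 with the pair (<, ≥), the same 0.905 with (≤, >), and 0.975 with the mixed pair (≤, ≥). A consistent shift of 1 mm only relabels the points.

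**Section 9.3.1.** Since F⁻(c − 1) = P(induration < c), the expression 1 − F⁻(c − 1) equals P(induration ≥ c) in healthy subjects, the false-positive rate. If specificity were 0.95, this formula would return 0.05. It contradicts both the < cut-off wording in its own sentence and the formula in section 12.1.

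**The case against.** The strongest defence is that ≤ x is no error. The Synopsis calls x an induration diameter, not a cut-off. The quantity is the empirical F⁻(x), which section 12.1 sets out to estimate and section 12.6 uses to size the trial, and section 12.1 supplies the mapping to the cut-off. All of this stands, and it defeats the claim, which a reader might infer, that the Synopsis estimator is in itself off by 1 mm.

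Two further inferences also fail. The smallest-negative wording does not produce a 1 mm shift: literally it gives 0 mm, and it reads as a slip for positive. Nor does the protocol inflate the ROC curve: that needs ≤ x for specificity and ≥ x for sensitivity at the same x, and no section prescribes this. Wherever the two measures are defined together, they use < and ≥ at one cut-off. Section 8.1 expects no C-Tb induration in this population, so k at any x ≥ 1 mm may well be small.

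The defence does not cover the contradictory cut-off definition in the primary objective, the missing link between x and the cut-off in the Synopsis, or the inverted formula in section 9.3.1.

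**Conclusion.** The point holds as a definitional inconsistency in the decision threshold and the primary estimate. Two statements are wrong as written: the outcome in the Synopsis cut-off definition and the formula in section 9.3.1. One is incomplete: the Synopsis estimator, which is a correct F⁻(x) but lacks its relation to the cut-off.

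The numerical consequence is conditional. It is zero if x is read as cut-off − 1. It is k/150, or 0.67 points per volunteer reading exactly x, if x is read as the cut-off. It reaches the ROC curve only if sensitivity is also counted at or above the same x. Because k is not given, no actual overstatement can be claimed. The equality between < c and ≤ c − 1 assumes readings in whole millimetres, in line with the integer grid in the Synopsis.

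**What to change.** 1. Synopsis, Trial objectives: change negative outcome to positive outcome, as in section 7.1.
2. Synopsis, Statistical methods: either define specificity at cut-off c as the relative frequency with C-Tb induration < c mm, or keep ≤ x and state that it is the specificity at cut-off c = x + 1. The first option is preferable because it matches the written definition and does not depend on whole-millimetre readings.
3. Section 9.3.1: replace 1 − F⁻(cut-off − 1) with F⁻(cut-off − 1), to match section 12.1.

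The cost is a few words in three places. Sample size, data collection and the precision table are unchanged.
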